# Effects of high-protein diet combined with exercise to counteract frailty in pre-frail and frail community-dwelling older adults: study protocol for a three-arm randomized controlled trial

**DOI:** 10.1186/s13063-020-04572-z

**Published:** 2020-07-11

**Keywords:** Frailty, Aging, High-protein diet, Protein supplementation, Resistance training, Strength training, Muscle power, Muscle strength, Muscle mass, Functional performance, Nutritional status

## Abstract

**Background:**

The proportion of older citizens is increasing worldwide. A well-known syndrome in old age is physical frailty which is associated with a greater risk of disabilities in activities of daily living, greater reliance on in-home services, hospitalization, institutionalization, and premature mortality. The purpose of this study is to determine the effects of an intervention with high-protein diet alone or in combination with power training in pre-frail and frail old adults.

**Methods:**

The study is a community-based assessor-blinded parallel randomized controlled trial (RCT), consisting of two phases. Phase 1 is a 1-month stabilization phase, where self-reliant community-dwelling adults + 80 years old will receive individual guidance regarding protein intake, to prevent the risk of negative protein balance prior to phase 2 and to only include participants who have reached the minimum recommended level of protein intake (1.0 g/kg/day) in the randomized controlled trial. Phase 2 is a 4-month RCT where 150 participants will be randomized into the following three arms: protein-only where participants will be provided with dairy products to increase their protein intake to 1.5 g/kg/day, protein + exercise where participants will be provided with the protein intervention in combination with power training two times a week, and recommendation group where participants will continue as in phase 1. Primary outcome is lower leg muscle power. Secondary outcomes include physical function and mobility, frailty status, muscle mechanical function, body composition, nutritional status, and health-related quality of life. The statistical analysis will include an intention-to-treat analysis of all randomized participant and per-protocol analysis of all compliant participants. The study hypothesis will be tested with mixed linear models to assess changes in the main outcomes over time and between study arms.

**Discussion:**

The finding of this study may add to the knowledge about the beneficial effects of high-protein diet from dairy products combined with power training to counteract frailty in community-dwelling older adults. This may ultimately have an impact on the ability to live well and independent for longer.

**Trial registration:**

ClinicalTrials.gov NCT03842579. Registered on 15 February 2019, version 1

## Background

The proportion of older citizens aged + 80 years old is increasing in the western population at faster rate than any other age group [1]. In Denmark, projections indicate that this group will represent 10% of the total population in 2060 from the current 4.4% [2].

Older age has been associated with greater prevalence of physical frailty a complex syndrome with multiple causes [3] characterized by reduced physiologic reserve and increased vulnerability to external and internal stressors [4]. The SHARE-FI75+ screening tool is specifically developed for + 75 years community-dwelling adults and operationalize non-frail, pre-frail, or frail condition by considering age, gender, and the presence of fatigue, low appetite, weakness, slowness, and low physical activity [5]. The prevalence of pre-frail and frail syndrome has been recently estimated as high as 43% between the age of 65 and 73 years using a slightly different screening tool earlier developed by Fried and colleagues [6], but data on the + 80 years old is still limited.

Physical frailty has been associated with greater risk of disabilities in basic and instrumental activities of daily living, chronic illnesses, loneliness, psychological distress, poorer self-reported quality of life, and premature mortality [7]. In addition, physical frail individuals have greater reliance on in-home services, risk for hospitalization, institutionalization, and overall greater health care cost [6, 8–11]. Hence, physical frailty has important implications for the individual older citizen as well as for the health care system.

One of the key determinants of this syndrome is the excessive loss of muscle mass which is strongly associated with the modifiable lifestyle factors, dietary protein intake and exercise [12, 13], both recognized as anabolic agents pivotal for primary, secondary, and tertiary prevention of physical frailty [14].

Specifically, diets high in protein are associated with a reduced risk of frailty [13]. Milk proteins are high-quality proteins with a high content of the amino acid leucine, known to effectively stimulate muscle protein synthesis [15, 16]. The current recommendation of total protein intake for older adults is minimum 1.0 g protein/kg/day based on European recommendations [12, 17], but it has been suggested that older adults, and especially frail older adults, can benefit from an even higher protein intake of 1.5 g protein/kg/day [18–20]. However, there is growing evidence that a large proportion of the older adults do not meet the recommendations for protein intake, e.g., due to anorexia of aging, medical conditions, and physical and mental limitations [12, 21, 22].

Exercise interventions focusing on strength and resistance training have been consistently shown to counteract the age-related decline of muscle function (e.g., muscle strength), physical function (e.g., walking speed) and disability among older adults [23, 24]. In addition, muscle power (the product of force times velocity) has been earlier considered a critical determinant to maintain function and independence in older age and exercise interventions targeting muscle power may play a key role in counteracting frail and pre-frail condition [25–27]. Several systematic reviews have investigated the beneficial effect of combining protein and exercise, but only one have examined the beneficial effect of protein alone [28] and none of the studies included in this review have used off-the-shelf dairy products or exercise interventions designed with muscle power components. Furthermore, it is unclear whether the combination of exercise and nutrition may be superior to the single interventions to improve physical performance in pre-frail and frail older adults as highlighted in a recent systematic review [29]. Possibly, the heterogeneity of the interventions (self-administered or supervised exercise programs, nutritional interventions range from supplements of selected micronutrients to protein supplementation from 10 to 30 g/day), duration, and settings (primary vs. secondary care settings) may have contributed to such unclear results [29]. Optimizing protein intake before initiating exercise may be essential for older adults who are not in protein balance to prevent the risk of an accelerated loss of muscle mass [30]. According to our knowledge, the benefit of optimizing protein intake before exercise interventions has not been examined before.

Therefore, the aims in this two phased parallel RCT is to investigate in pre-frail and frail older adults whether:
A.An increased protein intake from dairy products combined with power training increases (i) muscle power, and (ii) muscle mechanical function, maximal muscle strength, physical function, mobility, physical activity, muscle mass, health-related quality of life, and activities of daily living (iii) decrease pain, fear of falling, sedentary behavior, risk of malnutrition and (iv) modify physical frailty status and causes and contributors associated with such status.B.Protein and power training in combination has a superior effect compared to an increased protein intake from dairy products alone and to a third intervention based on current recommendations on diet and physical activity for older adults.

## Methods

### Study design

A 2-phase community-based assessor-blinded parallel RCT will be undertaken, to determine the effects of interventions with off-the-shelf dairy products alone or in combination with progressive power training, see Fig. 1.

**Fig. 1 Fig1:**
[figure not shown]
Flow-chart of the phases in the study (stabilization and intervention phases). RCT, randomized controlled trial; FU, follow-up; T, test session; g/kg/day, refers to g of protein/kg/day

### Study procedure

#### Inclusion criteria for participants

Participants are required to be (1) community-dwelling older adults + 80 years old; (2) pre-frail or frail, evaluated by SHARE-FI75+ [5]; (3) intact cognitive function, evaluated by a score ≥ 4 in the short form of the Mini-Mental State Evaluation (MMSE) [31, 32]; (4) medically stable as evaluated by medical screening (see details below); (5) able to participate in group-based exercise without need for transportation or individual exercise sessions; (6) signed informed consent; (7) able to speak and read Danish; (8) not allergic/intolerant to milk-products/protein; and (9) not on a weight losing diet.

#### Exclusion criteria for participants

Participants are excluded if they are not medical stable, including (1) eGFR < 40 ml/min/1.73 m^2^; (2) have received cancer treatment during the preceding 6 months; (3) received high doses of prednisolone and/or morphine, evaluated by medical doctor; and (4) have other medical issues that may affect the study.

#### Procedure for recruitment

Participants will be recruited through 3 pathways:
Nationally regulated preventive home visits service managed by the municipality, as earlier reported in [33]. Community-dwelling adults ≥ 80 years who are self-reliant in activities of daily living are offered a home visit by health-care personnel at least once a year. During the home visit, the older citizens will be informed about the study. As part of the preventive initiatives, the municipality may also invite groups of older citizens to presentations on selected health topics. When related to physical function, nutrition, or exercise, the I’m still standing study will also be presented.Existing cohort of community-dwelling older citizens (the Healthy Aging Network of Competence in Southern Denmark - Northern Schleswig-Holstein, HANC-study [33, 34]). All former participants will receive an invitation letter to the I’m still standing project.Advertisements in newspapers, on webpages, and social medias and presentations about the project at arrangements targeting older adults. All advertisements will be performed in close collaboration between the University of Southern Denmark and the Municipality of Odense targeting community-dwelling adults + 80 years and their relatives or health care personnel in primary prevention.

Recruitment to the project via all pathways is performed in collaboration with the municipality of Odense. The health care personnel will perform the screening for inclusion criteria (apart from the medical screening) and obtain informed consent from eligible participants.

##### Phase 1: Stabilization phase—1-month nutritional recommendation

The aim of the stabilization phase (phase 1) is to ensure that participants enrolled in the intervention (phase 2) will have a minimum daily protein intake according to the European recommendation, ≥ 1.0 g/kg/day [12] to prevent the risk of negative protein balance.

Risk of protein malnutrition in this phase will be first operationalized by the Protein Screener (Pro55+) [35] administered during the first home visit. The Protein Screener classifies participants according to the probability of being protein malnourished, with a probability above 30% considered as cutoff point for insufficient intake of protein. Different scenarios may occur during this phase:
Participants classified to have high probability of protein malnutrition (> 30%) by the Pro55+ will be individually guided to improve their intake of protein and receive publicly available material regarding nutritional guidelines specifically developed for older adults. One month later, participants will be asked to fill out a 4-day food record (three weekdays and 1 day during the weekend) to evaluate if the minimum requirement for daily protein intake is met.Participants classified to have a low probability of protein malnutrition (≤ 30%) by the Pro55+ will be immediately asked to fill out a 4-day food record (three weekdays and 1 day during the weekend). This step is to confirm that the average protein intake is ≥ 1.0 g/kg/day. If the 4-day food records indicate a protein intake below 1.0 g/kg/day, participants will be enrolled in the stabilization phase and an additional 4-day food records will be collected after 1 month.

Participants with a minimum intake of 1.0 g protein/kg/day will be invited to the medical screening. Participants not meeting the recommended protein intake after the stabilization phase will be followed as “natural observation group” but will not be considered for statistical purposes. They will receive two seminars on specific topics related to healthy aging and be asked to fill out self-reported questionnaires (at baseline and after 4 months) including demographic data, chronic diseases, activities of daily living, quality of life, appetite, nutritional status, sedentary behavior, function, pain and depression. Semi-structured interviews to identify potential barriers for not meeting the recommended level of daily protein intake will be conducted on a sub-group. The phases in the study are illustrated in Fig. 1.

#### Medical screening

The medical screening will be performed by a physician and will include blood pressure, auscultation of heart and lungs, blood sample, and an evaluation of medical history. Participants will be asked to bring their medications and direct count of name and dose will be performed. Medical stable is defined as no kidney diseases and eGFR ≥ 40 ml/min/1.73 m^2^, no cancer treatment within the last 6 months, no high doses of prednisolone and/or morphine, and no other medical issues that may affect the study.

##### Phase 2: Four months randomized controlled intervention

Eligible participants will be randomized into three groups: (i) protein-only group (PROT), (ii) protein + exercise group (EXEPROT), and (iii) recommendation group (REC).
PROT intervention

The PROT group will receive protein-rich off-the-shelf dairy products with the aim of targeting a daily protein intake of 1.5 g protein/kg/day. At baseline, individual supplementation plans are made based on information about participants habitual protein intake (assessed by the food records) and taste preferences. A cutoff of 15 g of supplementary protein is used—if participants have a higher requirement for protein, there will be a stepwise increase in protein intake over the first 4 weeks. Examples of products are skimmed milk, low-fat yoghurts with a high protein content (skyr), chocolate milk, cottage cheese, and ordinary low-fat cheese. Products will be delivered once a week at the home of the participant or at the training facilities. The type of products consumed may be changed throughout the study in order to avoid sensory-specific satiety and keep the compliance high. The PROT intervention is performed by specifically trained nutritional specialists.
2.EXEPROT intervention

The EXEPROT group will receive the same protein intervention as the PROT group combined with exercise program 1 h, twice a week. The exercise is designed as power training incorporating lower and upper body exercises with a training intensity of 65–80% of 1 repetition maximum (3 sets of 10–12 repetitions), which will be progressively adjusted throughout the entire intervention. Exercises will be performed explosively (i.e., as rapid as possible) during the concentric phase of the movement and controlled during the eccentric phase. At each session, participants register exercise activities, intensity, and rate of perceived exertion. The power training is performed by specially trained exercise specialists.
3.REC intervention

The REC group will be asked to follow the European recommendations for older adults on diet and physical activity over the course of the study and will be provided with publicly available material. In addition, two seminars on specific topics related to healthy aging will be provided to the group.

In all intervention groups, participants will continue with concomitant care and activities, e.g., if they have a rehabilitation plan including exercise. If participants experience changes in their medical condition, an additional consultation with the physician will be arranged to evaluate if participation in the study potentially will be harmful.

#### Compliance with the intervention

For the PROT and EXEPROT interventions, adherence to the protein protocol will be evaluated as average protein intake ≥ 1.35 g/kg/day at the 2 months and 4 months follow-up. Compliance and reasons for lack of compliance will also be estimated during each delivery of products with a set of questions (e.g., supplement consumption, changes to habitual food intake) and regular phone follow-ups. If participants are unable to reach the protein target, additional face-to-face or phone interview will be planned to support adherence. For the EXEPROT intervention, adherence to the exercise protocol will be considered as achieving minimum to 75% of valid exercise sessions, considered as minimum 70% of the exercises planned for each session. Reasons for non-adherence will be documented.

### Sample size determination

Muscle power is the primary outcome of this study. Due to lack of studies comparable to this study design (e.g., age and frailty status of the participants, type of exercise and level of protein supplementation), we have calculated sample size using a combination of studies and methods. Based on findings by Bechshøft et al. [36], the effect of 12 weeks of protein supplementation (two daily supplements of 20 g milk protein) in combination with resistance training in + 80-year-old healthy adults increased muscle power by 15% (SEM ± 5%) in comparison with − 7% (SEM ± 6%) in the control group (receiving protein supplementation only). In the study by Park et al. [37], 12 weeks of protein supplementation (0.8 g/kg/day, 1.2 g/kg/day, or 1.5 g/kg/day) to pre-frail or frail older adults above 70 years resulted in an increase in muscle mass (estimated by DXA) of approximately 4% in the group receiving 1.5 g/kg/day. Unpublished data from our own group shows that change in muscle mass (estimated by DXA) accounted for 1.95% of the change in muscle power (power-rig) in older adults following 12 weeks of explosive resistance training. Hence, the estimated effect of an increase in muscle mass of 4% on muscle power is 7.8%. Adding this to the results from Bechshøft et al. [36] gives us an estimated change on 0.8% in the PROT group. Assuming that the change in muscle mass are comparable in the three groups, we therefore expect a change in muscle power of 15%, 0.8%, and − 7% with a SD of 30 in the EXEPROT, PROT, and REC groups, respectively.

Setting a power of 0.8 a sample size with 37 participants in each arm should be enough to detect a significant difference in muscle power (significance level at 0.05). Adding 25% to account for dropouts a total of 150 participants is needed.

Strength calculation was made in PASS 14.

### Randomization and blinding

After the baseline assessment, each participant will be randomized to one of the three study groups (PROT, EXEPROT, or REC) using a computer-based random-block randomization scheme, clustering by couples when cohabitees wish to be enrolled together. The code is generated, concealed (sealed envelopes), and stored by personnel who is not part of run of the study. This personnel reveals the allocation to interventions based on ID numbers only to the research assistants who will inform participants. The trial has an open design with blind assessment of outcomes, which means that participants will be asked not to reveal group allocation when undergoing follow-up measurements, as researchers conducting follow-up measurements will be blinded to group allocation. To assess the extent to which blinding has been preserved, researchers will record the number of cases in which allocation was revealed.

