### Statistical analysis

Plans for data entry, coding, security, and storage including any related processes to promote data quality have been approved by the Danish Regional Data Protection Agency. The full analysis set will follow an intention-to-treat principle and will include all randomized participants. The study hypothesis will be tested with mixed linear models to assess changes in the main outcomes over time and between study arms controlling for confounders (e.g., age, sex, lifestyle factors). Per-protocol analysis of participants that are compliant to the protocol will be performed. Lastly, if sample size allows it, sub-group analysis by sex and by habitual lifestyle (protein intake and physical activity) will be performed based on baseline assessment. Wilcoxon signed rank sum test, Mann-Whitney *U* test, and odds ratio or chi-square test of relationships were used when appropriate. The statistical software programme STATA 16 (StataCorp. 2019. *Stata Statistical Software: Release 16*. College Station, TX: StataCorp LLC) will be used for the statistical analysis.

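### Couples who enrol together are randomised as a unit, but the sample size makes no allowance for this and the described analysis names no couple term

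*Protocol article*

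**What the plan says.** Three sections of the protocol article bear on this.

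- **Randomization and blinding.** Participants are allocated to one of three arms by a computer-generated block scheme, "clustering by couples when cohabitees wish to be enrolled together". Partners who enrol together therefore receive the same arm. Everyone else is allocated singly.
- **Sample size determination.** The inputs are expected changes in muscle power of 15%, 0.8% and −7%, "with a SD of 30 in the EXEPROT, PROT, and REC groups, respectively". The result is that "a sample size with 37 participants in each arm should be enough" at a power of 0.8, with "significance level at 0.05". An allowance for dropout brings the total to 150. No couple share, within-couple correlation or design effect appears.
- **Statistical analysis.** "The study hypothesis will be tested with mixed linear models to assess changes in the main outcomes over time and between study arms", with control for confounders such as age, sex and lifestyle factors. Wilcoxon signed rank, Mann-Whitney and chi-square tests or odds ratios are listed for use where appropriate. No couple term is named, and no random-effects structure is given.

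The limitations section comments on the power calculation but does not mention couples.

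**The concern.** When two people are allocated together, they do not supply two independent pieces of information about the difference between arms unless their outcomes are uncorrelated. The unit of randomisation should be reflected in the variance of every arm comparison. If it is not, and partners' changes are positively correlated, confidence intervals are too narrow, the type I error rate exceeds the nominal 5%, and true power falls below the planned figure.

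Positive correlation is plausible for people who share a household, perhaps most of all for diet outcomes. The protocol does not state or estimate it for any outcome.

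At stake are the primary comparison of leg muscle power and the secondary comparisons. The rank and chi-square tests need particular attention: in standard form they assume independent participants and have no place for a couple effect.

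**Working it through.** **1. Reproduce the stated sample size.** The inputs, all from Sample size determination, are means 15, 0.8 and −7, SD 30, alpha 0.05 and power 0.8. The test is not named. I took a one-way three-group F test on independent participants.

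- Grand mean: (15 + 0.8 − 7)/3 = 2.933.
- Sum of squared deviations: 12.067² + 2.133² + 9.933² = 248.8.
- Noncentrality: n × 248.8/30² = 0.2765n.
- n = 36 gives power 0.802; n = 37 gives 0.813.
- Dropout: 37/0.75 = 49.3, rounded up to 50 per arm, so 150 in total.

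Pairwise two-sided t tests do not give 37. They need 30 per arm (15 against −7), 71 (15 against 0.8) and 233 (0.8 against −7). The stated figure is therefore accounted for, within one participant per arm, by an overall test on independent individuals, with no sign of a couple allowance.

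**2. Design effect for a mix of pairs and singles.** Let f be the share of an arm's participants who are in couples and ρ the within-couple correlation of change. An arm of n participants contains fn/2 couples, and each adds 2ρσ² to the variance of the sum:

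variance of the sum = nσ² + (fn/2) × 2ρσ² = nσ²(1 + fρ).

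The design effect is 1 + fρ, and the true standard error is √(1 + fρ) times the one that ignores couples.

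**3. Consequences.** Neither f nor ρ is in the document, so both are assumptions shown as a range.

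- Type I error if couples are ignored, for a two-sided comparison of two arms (normal approximation): 2 × [1 − Φ(1.96/√(1 + fρ))].
- Power at 37 per arm: the F test above with the noncentrality divided by 1 + fρ.
- Participants needed per arm: 36 × (1 + fρ), rounded up, then divided by 0.75 for dropout.

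| f | ρ | Design effect | True SE vs naive SE | Type I error | Power at 37 per arm | Needed per arm (total with dropout) |
|---|---|---|---|---|---|---|
| 10% | 0.1 | 1.01 | +0.5% | 5.1% | 0.809 | 37 (150) |
| 20% | 0.3 | 1.06 | +3.0% | 5.7% | 0.789 | 39 (156) |
| 40% | 0.5 | 1.20 | +9.5% | 7.4% | 0.734 | 44 (177) |

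As an outer bound only, 100% in couples with ρ = 0.5 gives a design effect of 1.50, type I error of 11.0% and power of 0.630.

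**4. Which couple effect matters.** The primary outcome is measured at T3 and T5, and the question is the difference between arms in change. A couple effect that is constant over time appears at both visits and cancels from the change. A couple random intercept alone therefore leaves correlated change unmodelled. The couple effect has to vary with time, or the standard errors have to be made robust at couple level.

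**The case against.** The strongest reply is that the Statistical analysis section is silent rather than wrong. It names mixed models without specifying any random effects, and a mixed model is a natural place for a couple effect. That detail is often left to a statistical analysis plan, which is not at hand. A reader might infer that the model treats every participant as independent and that the trial's standard errors are too small. The document does not support that: it neither states independence in the analysis nor rules out a couple term. It also plans adjustment for lifestyle factors, which could absorb part of any similarity between partners.

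A reader might also suppose that partners share meals, products and training. The protocol does not say so. Supplementation plans are individual, based on each person's habitual intake and taste; dairy products go only to two arms and training to one.

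Finally, the effect may be very small. Clusters have at most two members, and the eligibility criteria (80 or older, pre-frail or frail, cognitively intact, medically stable, protein intake of at least 1.0 g/kg/day) make a high couple share unlikely. If no one dropped out, 50 per arm would give power 0.862 even at 40% and 0.5.

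These replies limit the claim to a conditional one. They do not remove it. The sample size is a protocol item and has no couple allowance. The listed rank and chi-square tests in standard form cannot reflect the allocation. Power at 37 per arm is only 0.813, so there is little slack.

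**Conclusion.** The point holds in conditional form. It is established that couples are allocated as a unit, that the stated sample size matches a calculation for independent participants, and that the described analysis names no couple term. It is not established that the final analysis will ignore couples, or that partners' changes are correlated.

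If couples are left out and the correlation of change is positive, the understatement of the standard error ranges from trivial to modest over the assumed range: design effect 1.01 to 1.20, type I error 5.1% to 7.4%, power 0.81 to 0.73. With 20% in couples and a correlation of 0.3, power falls just below the planned 0.8. These figures also assume similar couple shares in each arm and the overall F test as the basis of the stated sample size. The correction is worth making because it is nearly free and brings the analysis into line with the randomisation, not because a serious bias has been shown.

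**What to change.** - Record a couple identifier for every participant, with people enrolled singly as clusters of one.
- In every arm comparison, either use cluster-robust standard errors on the couple identifier or add a couple-by-time random effect above the participant level. A couple intercept alone is not enough.
- Where a Mann-Whitney or chi-square comparison of arms was intended, use a method that respects the couple, such as a regression model with couple-robust standard errors.
- Report the number of couples in each arm.
- In the sample-size text, note that the stated 80% power assumes no couple clustering, and give the design effect 1 + (share in couples × correlation) with the expected share.

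The cost is one data field and about one line of model code. Intervals become slightly wider when partners' changes are positively correlated.
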